## 10.2. The Number of Participants

The sample size is 1856 high-risk women (928 to be recruited in The Gambia and India). The study was powered to have 80% to detect a 33% reduction in the incidence of GDM, for the main effects of diet and PA, with a family-wise significance level of 5% for a two-sided test (i.e. each effect was tested at a significance level of 2.5%). It was assumed that participants could be pooled across centres (no interaction between interventions and country at the 5% level). The sample size was inflated to allow for a 15% drop out rate in each of the four strata, with drop outs defined as non-compliant participants (i.e. no risk reduction in their incidence of GDM).

The effect sizes for the sample size calculation were:

Prevalence of GDM in high-risk pregnant women: The largest study of GDM women (The HAPO study, 25,505 pregnant women unselected for GDM risk at 15 centres in nine countries) reported a GDM prevalence rate, based on IADPSG criteria, of 17.8% among the general population. In our 'high-risk' population, we assume that the prevalence will be higher than in the HAPO study. Therefore, we have estimated the prevalence of 25% in our study.

Estimated risk reduction: A recent meta-analysis (Song et al. Obesity reviews 2016) has shown that either diet or PA results in 18% (95% CI 5-30%) risk reduction in GDM in general pregnant population and interventions as early as 15 weeks of gestational age was also associated with reduced GDM risk (Relative risk: 0.80, 95%CI 0.66-0.97). Putting all these together, we estimate the risk reduction would be higher (about 1/3, 33%) in this high-risk population. We modelled the GDM percentages in four equal-sized combinations of control (c) and treatment (t) arms as 25% (c-c), 16.75% (c-t and t-c) and 11.2 in t-t group. Therefore, in simple comparisons of one exposure, the percentages will be 20.9% vs 13.0%.

Absence of intervention\*country interaction: In order to pool the participants of both countries, we will be assuming that there are no differences between the participants of both countries. This initial test for a non-significant interaction term (at the 5% level) between each intervention and country was also taken into account in the sample size simulation.

The sample size calculation was performed by simulation (in R version 3.5.2) according to the following algorithm:

1. For a given sample size, we generated 8 subgroups, two (one per country) for each intervention combination (control-control, treatment1-control, control-treatment2, treatment1-treatment2).
2. For each subgroup we generated the expected GDM incidence, except for a random 15% (drop-outs), whose expected GDM incidence was considered to be 25% (corresponding to the control group) regardless of their originally allocated subgroup.

Date and version No: 18th July 2019, Version 4.2

3. We first tested if either the interaction term site\*PA or site\*Yoghurt was statistically significant (at the 5% level).
4. If the assumption of no intervention\*country interaction was met, we recorded for each intervention if it was statistically significant (at the 2.5%, as we were doing two tests, one for each intervention), assuming a two-sided test
5. This was repeated 10,000 times.
6. The % of repetitions with statistically significant intervention effects represents the power associated with the sample size.
7. Steps 1-6 were repeated for increasing sample sizes.
8. A smoothed (lowess) line was fitted.
9. The point where this line crossed the 80% power mark gave us the final sample size required. (Figure 1)

[figure not shown]

Figure 1: Estimated power for increasing sample size, with an estimated risk reduction of 33%,  $\alpha = 0.05$  and estimated drop-out rate of 15% (based on 10,000 iterations).

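### Section 10.2 puts a country-interaction gate in front of the pooled test that section 10.3.1 does not have; the gate costs 4 to 8 points of power, and the 15% drop-out margin leaves nothing for missing outcomes

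*Protocol*

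**What the plan says.** Protocol section 10.2 sets the target: "The study was powered to have 80% to detect a 33% reduction in the incidence of GDM", for the main effects of diet and of physical activity. On level it says that "each effect was tested at a significance level of 2.5" per cent, two-sided. On numbers: "The sample size is 1856 high-risk women (928 to be recruited in The Gambia and India"). The modelled GDM percentages are "25% (c-c), 16.75% (c-t and t-c) and 11.2 in t-t group".

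Pooling over the two countries is made conditional: "This initial test for a non-significant interaction term (at the 5% level) between each intervention and country was also taken into account" in the simulation. In the algorithm, step 3 asks whether *either* of the two site-by-intervention terms is significant at 5%. Step 4 records each intervention's result at 2.5% if the no-interaction assumption was met. Step 6 reads: "The % of repetitions with statistically significant intervention effects represents the power associated with the sample size". Step 5 sets 10,000 repetitions.

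The sample is inflated for 15% drop-out, "with drop outs defined as non-compliant participants". Step 2 gives these women an outcome, "whose expected GDM incidence was considered to be 25% (corresponding to the control group) regardless of their originally allocated subgroup".

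Section 10.3.1, on the primary outcome, estimates the effect on GDM by binary regression. It adds that the difference in effect between centres will also be tested, as the ratio of the two countries' odds ratios. It does not make the main-effect analysis depend on that test.

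**The concern.** Three things do not fit together.

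1. **The rule.** Section 10.2 lets an intervention effect count only after a preliminary test is passed; section 10.3.1 has no such rule. Power was therefore computed for a procedure that the primary-analysis section does not describe.
2. **The algorithm.** The general text speaks of a test for each intervention, while step 3 speaks of either term. The document does not say clearly whether one significant interaction blocks one intervention or both, nor whether blocked repetitions stay in the denominator of step 6. A reader who codes steps 3 and 4 as written does not get 80%.
3. **The drop-out margin.** The 15% covers dilution by women who are measured but do not comply. Section 7.6.1 withdraws women after randomisation for scan findings, section 7.9 foresees loss to follow-up, and section 7.8.1 says withdrawals are not replaced. Outcomes that are never observed have no allowance.

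At stake is a few points of power given up for a pre-test that will fire by chance, and an ambiguity about the primary test that could be settled after the interaction result is known.

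**Working it through.** **Inputs (all from section 10.2).** 1,856 women, so 928 per level of each factor and 232 per country-by-arm cell. Arm rates 25%, 16.75%, 16.75% and 11.2%, the same in both countries. 15% non-compliers at 25%. Two-sided 2.5% per intervention. Interaction tests at 5%.

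**Dilution.** Rate = 0.85 × arm rate + 0.15 × 25%:
- control–control: 25.0%
- one intervention: 0.85 × 16.75 + 3.75 = 17.99%
- both: 0.85 × 11.2 + 3.75 = 13.27%

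Margins: (25.0 + 17.99)/2 = 21.49% against (17.99 + 13.27)/2 = 15.63%, a difference of 5.865 points before rounding. (Section 10.2 summarises the undiluted treated margin as 13.0%, but the mean of 16.75 and 11.2 is 13.98. The arm rates are used here.)

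**Main-effect power without a gate.** Power = Φ[(difference − z × SE₀)/SE₁], with z = 2.241, pooled SE₀ = √(2 × 0.1856 × 0.8144/928) = 0.01805 and unpooled SE₁ = √((0.2149 × 0.7851 + 0.1563 × 0.8437)/928) = 0.01800. This gives Φ[(0.05865 − 0.04046)/0.01800] = Φ(1.011) = 84.4%.

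**Effect of the gate when effects are identical.** Each interaction test rejects 5% of the time by chance. Treating the tests as independent of each other and of the main effect:
- own interaction only: 0.844 × 0.95 = 80.2%
- either blocks both: 0.844 × 0.95² = 0.844 × 0.9025 = 76.2%

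**Simulation** of the eight-cell algorithm (logistic regression, Wald tests, 40,000 repetitions, 1,856 women). At least one interaction was significant in 9.8% of repetitions.

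| Rule | Analytic | Simulated | Analytic N for 80% |
|---|---|---|---|
| No gate | 84.4% | 84.8% | 1,670 |
| Each effect blocked by its own interaction | 80.2% | 80.5% | 1,848 |
| Either interaction blocks both, blocked runs count as failures | 76.2% | 76.4% | 2,088 |
| Either blocks both, blocked runs left out of the denominator | – | 84.7% | – |

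The second row reproduces the plan's figure: 80% at 1,856, with a solved N of 1,848. The third row is the literal wording of steps 3 and 4 with all 10,000 repetitions in the denominator. The cost of the gate is 84.4 − 80.2 = 4.2 points or 84.4 − 76.2 = 8.2 points.

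**Missing outcomes.** The protocol gives no rate, so 5%, 10% and 15% are assumed, spread evenly and on top of the 15% non-compliance. The number per margin falls to 928 × 0.95 = 882, 928 × 0.90 = 835 and 928 × 0.85 = 789.

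| Missing | No gate, analytic | Own gate, analytic (× 0.95) | Rounded, simulated: no gate / own gate |
|---|---|---|---|
| 5% | 82.3% | 78.2% | 83% / 79% |
| 10% | 80.1% | 76.1% | 80% / 76% |
| 15% | 77.5% | 73.7% | 78% / 74% |

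With the either-blocks-both gate, 10% and 15% missing give about 73% and 70%.

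**The case against.** The strongest answer is that the stated 80% can be reproduced. The text of section 10.2 describes the test as one for each intervention, and step 4 records results intervention by intervention. On that reading the loss is 5%, power is 80.2–80.5%, and the sponsor has already paid for the gate by going from about 1,670 women to 1,856. This stands. A reader might infer from steps 3 and 4 that true power is 76% and the trial is too small; the documents do not support that, because 76% is one reading of an ambiguous algorithm and not the likeliest account of what was run.

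Second, a reader might infer that a chance interaction would leave the trial without a primary result. That goes too far as well. The gate appears only in the sample-size section, section 10.3.1 states the analysis unconditionally, and any fallback could sit in a statistical analysis plan that is not shown. What remains is that the two sections of this document disagree on whether the main-effect test is conditional.

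Third, the definition of drop-outs as non-compliers is open, and section 7.8.2.2 requires follow-up of all women whatever happens to their intervention. Modelling non-compliers as observed suits an intention-to-treat analysis. But it does not cover women whose outcome is never obtained, and the protocol itself expects some.

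**Conclusion.** The point holds as an inconsistency and an avoidable loss, not as a demonstrated error in the sample size. At 1,856 women and with the stated inputs, the pooled main effect has about 84–85% power per intervention. The gate lowers this to about 80% (own interaction) or about 76% (either interaction, as steps 3 and 4 read), although effects are assumed identical in both countries. The 80% is reproducible under the first of these rules, but not by following steps 3 and 4 as written.

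Nothing is reserved for missing outcomes. Under the rule that reproduces 80%, even 5% missing brings power to about 79%; without the gate, power stays at about 80% with 10% missing. These figures rest on the protocol's rates and non-compliance model, and on missing proportions that are assumptions of this review. The matter is a worthwhile, inexpensive improvement and does not put the trial's size in question.

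**What to change.** - In sections 10.2 and 10.3.1, state that the primary test of each intervention is the pooled, centre-stratified main effect at the 2.5% level, carried out whatever the country-interaction test shows.
- Report the Gambia:India ratio of odds ratios with its confidence interval, and the country-specific estimates, as secondary results.
- Restate power per intervention at 1,856 as about 84% with complete outcomes, and about 80% and 78% with 10% and 15% of outcomes missing, keeping non-compliance and missing outcomes as separate allowances.
- If the gate is kept, correct steps 3, 4 and 6 to the rule actually simulated: which interaction blocks which effect, and how blocked repetitions are counted. Make section 10.3.1 agree.

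The cost is wording in two sections and one rerun of the simulation, with no extra women. The downside is that if effects truly differ by country, the pooled estimate is an average over the two, so the country estimates must always be shown beside it.

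### Testing each main effect at a fixed 2.5% is valid but inefficient; Holm keeps the 5% family-wise limit and adds about 4.5 points of power per intervention

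*Protocol*

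**What the plan says.** Protocol section 10.2 sets the error rate at "a family-wise significance level of 5% for a two-sided test (i.e. each effect was tested at a significance level of 2.5" per cent. Step 4 of the simulation algorithm in that section applies the same level: "we recorded for each intervention if it was statistically significant (at the 2.5%, as we were doing two tests, one for each intervention". Neither place lets the level for one intervention depend on the result for the other, and no step-down rule appears elsewhere in the protocol.

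The power target is per effect: "The study was powered to have 80% to detect a 33% reduction in the incidence of GDM, for the main effects of diet and PA". The design scenario has both interventions working, with GDM percentages of "25% (c-c), 16.75% (c-t and t-c) and 11.2 in t-t group". Step 3 adds a preliminary check: "We first tested if either the interaction term site\*PA or site\*Yoghurt was statistically significant (at the 5% level".

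Section 10.3.1, on the primary outcome, gives no test level for the final analysis and plans 95% confidence intervals.

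**The concern.** The stated aim is a 5% family-wise error rate over two tests. Giving each test 2.5% regardless of the other result meets that aim but does not use all the error allowed. Once one null hypothesis has been rejected at 2.5%, only one remains, and it can be tested at the full 5% without the family-wise rate exceeding 5%. That is Holm's procedure. It never rejects less than the fixed split.

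The unused error matters most when both interventions are effective, which is the scenario in section 10.2. There, a trial with one p-value below 2.5% and the other between 2.5% and 5% would report one real effect and miss the second. That second effect could have been claimed within the same error limit and with no extra participants.

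**Working it through.** **Inputs (all from protocol section 10.2).** The total is 1,856 women in eight equal country-by-arm cells of 232, so each main effect compares 928 with 928. (The synopsis gives 1,875; I use the figure attached to the power statement.) Cell risks are 25%, 16.75%, 16.75% and 11.2%; the last is 25 × 0.67² = 11.2225% before rounding. A random 15% of each cell carries a 25% risk whatever the arm. Main effects are tested two-sided at 2.5% and country interactions at 5%.

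**Risks after non-compliance.**
- Single-intervention cells: 0.85 × 16.75 + 0.15 × 25 = 17.99%.
- Combined cell: 0.85 × 11.2225 + 0.15 × 25 = 13.29%.
- Margin without the intervention: (25 + 17.99)/2 = 21.49%.
- Margin with it: (17.99 + 13.29)/2 = 15.64%.

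**Power before the country check.** The difference is 0.2149 − 0.1564 = 0.0585. The standard error is √[(0.2149 × 0.7851 + 0.1564 × 0.8436)/928] = 0.0180. The ratio is 3.25, and 3.25 − 2.24 = 1.01, which gives about 84% power. Simulation with main-effects logistic regression and Wald tests gives 84.5%.

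**Reproducing the plan's 80%.** With no true interaction, each interaction test passes about 95% of the time.
- Each effect needs only its own interaction to be non-significant: 84.5% × 0.95 = 80.3%. Simulation gives 80.2% to 80.4%, so the stated 80% reproduces.
- Both interactions must be non-significant: 84.5% × 0.95² = 76.3%. Simulation gives 76.2%.

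**Effect of Holm: analytic check.** Suppose power is 80% at the 2.5% level. The shift is 2.241 + 0.842 = 3.083, so power at the 5% level is Φ(3.083 − 1.960) = 86.9%. Treating the two tests as independent:
- Each effect: 0.800 + (0.869 − 0.800) × 0.800 = 85.5%.
- Both effects, fixed split: 0.80² = 64.0%.
- Both effects, Holm: 0.869² − (0.869 − 0.800)² = 75.1%.

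**Effect of Holm: simulation at N = 1,856** (40,000 to 60,000 repetitions). The same p-values are judged under both rules. An intervention that fails the country check counts as not significant.

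| Country check | Each effect, fixed 2.5% | Each effect, Holm | Both effects, fixed 2.5% | Both effects, Holm |
|---|---|---|---|---|
| Own interaction only | 80.2% | 84.6% | 64.3% | 73.2% |
| Both must pass | 76.2% | 80.6% | 64.3% | 73.2% |
| None | 84.5% | 89.3% | 71.5% | 81.1% |

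The gain is about 4.4 to 4.8 points per effect and 9 to 10 points for both. Repeat runs differ from these figures by a few tenths of a point.

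**In participants.** With the own-interaction check, the fixed split reaches 84.4% per effect at 2,080 women and 73.4% for both at 2,160. Matching Holm at 1,856 would therefore take roughly 220 (2,080 − 1,856 = 224) to 300 (2,160 − 1,856 = 304) more women.

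**Error rates under Holm, no country check.** Family-wise error is 4.9% when neither intervention works and about 4.8% when one works. In the second case the fixed split gives about 2.5%, because only one true null is tested, at 2.5%.

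**Where there is little or no gain.** Power to show at least one effect is the same under both rules (97.5% with no country check). If only one intervention works, its power is about 93% with no country check and rises by about 0.1 point.

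**The case against.** - **Two valid procedures.** The fixed split controls family-wise error at 5% exactly as stated, so nothing in the section is wrong or contradictory. This stands. A reader might infer that the 2.5% level is a mistake or leaves the trial underpowered. The documents support neither: the stated 80% reproduces under one natural reading of the algorithm.
- **Not necessarily the final rule.** The 2.5% level appears only in the sample-size section, describing the simulation. Section 10.3.1 gives no level, and an analysis plan not shown here may set one. This also stands, so one cannot say that the final analysis is bound to the fixed split. But 2.5% is the only level the protocol states, and a step-down rule has to be fixed before results are known.
- **Not free.** A reader might infer that Holm has no cost or leaves every error rate unchanged. It does not. The 5% limit holds, but when one intervention works the false-positive chance for an ineffective partner nearly doubles, from about 2.5% to just under 5%. Intervals that match Holm are also less simple than a pair of 97.5% intervals.
- **The gain depends on the scenario.** The protocol sets no target for showing both effects, and the quoted gains need both interventions to achieve the full 33%. The section itself cites a pooled reduction of 18%. If each achieved only that, the gain with no country check would be about 4 points per effect and 7 to 8 points for both. The gain is smaller but does not disappear.

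**Conclusion.** The point holds as a cheap improvement. The fixed 2.5% split in section 10.2 is valid but needlessly inefficient, because Holm meets the same 5% family-wise limit at the same sample size and rejects everything the split rejects.

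With the country-interaction check, Holm adds about 4.5 points of power per intervention and about 9 points for showing both. This rests on the plan's own assumptions: 1,856 women, a 33% reduction from each intervention with multiplicative joint effect, 15% non-compliant at control risk, and no true interaction with country. The benefit is confined to trials in which both interventions work. It does not raise the chance of finding at least one effect.

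**What to change.** In section 10.2, amend the rule of 2.5% per effect. In section 10.3.1, where there is no such wording to replace, insert: *The smaller of the two main-effect p-values is tested at 2.5%; if significant, the other is tested at 5% (Holm).* Do this before any unblinded comparison is seen.

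Three details should go with it:
- Keep the sample size and restate the power under Holm, saying which reading of the country check applies (own interaction only, or both).
- Say what happens to an intervention that fails the check. The figures above count it as not significant and keep the family at two tests.
- State which confidence interval accompanies each step, and that pairing a 97.5% with a 95% interval does not give simultaneous 95% coverage. This needs settling anyway, because 95% intervals beside 2.5% tests can exclude no effect while the test is not significant.

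The cost is a few sentences in the protocol and the analysis plan, with no added recruitment. The sponsor accepts the higher false-positive chance for an ineffective second intervention, still within the 5% family-wise limit.

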| Short Study Title (to be used on participant-facing documents, if applicable) | PRIMORDIAL Study                                                                                                                                                                                                                                            |                                                                                                                                                                                                                                                                                                                                                                                                            |
| Nature of Study Participants                                                  | Pregnant women with high-risk for developing gestational diabetes                                                                                                                                                                                           |                                                                                                                                                                                                                                                                                                                                                                                                            |
| Intended number of participants                                               | 1,875 high-risk women (~937 from each centre)                                                                                                                                                                                                               |                                                                                                                                                                                                                                                                                                                                                                                                            |

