### 7.8.1. Discontinuation/Withdrawal from the study

Discontinuation from the study occurs

- When a participant voluntarily withdraws consent to further participation at any time during the trial.

Date and version No: 18th July 2019, Version 4.2

- Significant protocol deviation such as Ineligibility (either arising during the study or retrospectively having been overlooked at screening)
- Loss to follow-up

Details of withdrawing/discontinuation from the study prior to completion of all scheduled visits should entered in the “study termination form”

Participants who are diagnosed to have GDM (by laboratory evidence within the protocol or outside diagnosis confirmed by an OGTT at study centre) should continue interventions till week 32 (end of study visit), unless there is a safety concern.

Temporary or permanent discontinuation of interventions (as detailed in sections 7.8.1 and 7.8.2) for safety reasons will not lead to withdrawal of the participant from the trial. Withdrawal of the participants will not be replaced by recruitment of new participants. The primary reason for withdrawal will be specified in the Case Report Form.

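### The 15% drop-out allowance in section 10.2 models non-compliance with the outcome observed; there is no term for women without a GDM result

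*Protocol*

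**What the plan says.** Protocol section 10.2 gives the target and the power: "The sample size is 1856 high-risk women (928 to be recruited in The Gambia and India"), and "The study was powered to have 80% to detect a 33% reduction in the incidence of GDM, for the main effects of diet and PA". It says the number was inflated for a 15% drop-out rate, "with drop outs defined as non-compliant participants (i.e. no risk reduction in their incidence of GDM").

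Step 2 of the simulation in the same section carries this out. A random 15% of each subgroup are drop-outs, "whose expected GDM incidence was considered to be 25" per cent whatever their arm. No step removes anyone. The final number is read off where the fitted power curve crosses 80%.

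Other sections describe women who leave without a GDM result:

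- Section 7.9 defines loss to follow-up by the absence of any efficacy endpoint data.
- Section 7.6.1 withdraws women with certain scan findings at 18-20 weeks, before the OGTT at 26-28 weeks.
- Section 7.8.1 lists consent withdrawal and ineligibility found later, and adds: "Withdrawal of the participants will not be replaced by recruitment of new participants".

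The synopsis gives a slightly different target, "1,875 high-risk women (~937 from each centre"), without explanation.

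**The concern.** Non-compliance and a missing outcome affect a trial differently. A non-compliant woman who is followed dilutes the treatment effect but still counts in the denominator. A woman with no OGTT or week-32 glucose reduces the number analysed. Section 10.2 provides for the first and is silent on the second, although sections 7.6.1, 7.8.1 and 7.9 create the second.

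Because the size was set at the 80% crossing point, there is little slack for a further loss. The DSMC is charged in section 12.1 with reviewing loss to follow-up. It could read the 15% as the attrition the trial was sized to absorb in addition to non-compliance, when the calculation contains no such margin.

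**Working it through.** **Inputs, all from section 10.2.** N = 1,856, so 928 against 928 for each main effect. Cell risks: "25% (c-c), 16.75% (c-t and t-c) and 11.2 in t-t group". Drop-outs: 15%, at 25% risk. Two-sided level: "each effect was tested at a significance level of 2.5" per cent, so z = 2.2414. A 5% intervention-by-country test precedes each main-effect test. The rate of missing GDM results is not stated, so 5-15% is assumed.

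**Step 1: diluted risks, p' = 0.85p + 0.15 × 0.25.**

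- Control-control: 25.0%.
- One intervention: 0.85 × 0.1675 + 0.0375 = 17.99%.
- Both: 0.85 × 0.1122 + 0.0375 = 13.29%, with 0.1122 = 0.25 × 0.67².
- Margins: (25.0 + 17.99)/2 = 21.49% against (17.99 + 13.29)/2 = 15.64%.

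**Step 2: reproduce the plan's figure.** With n per side, difference Δ = 0.05855 and mean risk p̄ = 0.18566,

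power = Φ{[Δ√n − z√(2p̄(1−p̄))] / √(pC(1−pC) + pT(1−pT))}.

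At n = 928 this is Φ{(1.7837 − 1.2325)/0.5483} = Φ(1.005) = 0.8426. Each effect must also pass its own country-interaction test, which happens with probability 0.95 when there is no interaction: 0.8426 × 0.95 = 0.8005. The smallest N that reaches 80% is 1,854. A logistic-regression simulation of 40,000 runs at 1,856 gave 80.1%.

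Other readings do not return 1,856:

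- No interaction test: 84% at 1,856, and 80% needs 1,674.
- Both interaction tests must pass: 76% at 1,856, and 80% needs about 2,096. The wording of the algorithm could allow this, but that is a separate matter.
- The 15% removed as missing, no dilution: about 1,500 would suffice.

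So the stated number rests on all 1,856 women having an outcome.

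**Step 3: missing results on top of 15% non-compliance.** Replace n by 928(1 − f) and keep the diluted risks and the factor 0.95.

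| Missing f (assumed) | Scored women | Power |
|---|---|---|
| 0% | 1,856 | 80.05% |
| 5% | 1,763 | 78.1% |
| 10% | 1,670 | 75.9% |
| 15% | 1,578 | 73.5% |

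Simulation agrees within a point: 78.3%, 76.7% and 73.5% for the last three rows.

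**Step 4: missing results within the 15%.** Here the non-compliance share applies to the scored women.

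| Non-compliant | Missing | Power |
|---|---|---|
| 10% | 5% | 82.9% |
| 5% | 10% | 85.1% |
| 0% | 15% | 86.9% |

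Dilution costs more power than loss, so moving women from the first category to the second raises power.

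**Step 5: the synopsis figure.** 1 − 1,856/1,875 = 1.0%. The larger target would offset about 1% missing, and nothing says it was meant to.

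**The case against.** The arithmetic of section 10.2 is sound on its own terms. The term drop-out appears only in the sample-size text and its figure caption, where it is expressly defined; sections 7.8 and 7.9 use other words. So the protocol does not use one term in two senses. The handling of missing outcomes under intention-to-treat may properly sit in the SAP, which is not shown. All of this stands. What remains is that section 10.2 itself fixes the number, the power and the allowance, and has no term for unscored women.

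Three stronger readings are tempting, and the documents do not support them:

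- A reader might infer that 80% power fails if the 15% is ordinary attrition. It does not: with 15% missing and no dilution, power is about 87%, or about 83% if both interaction tests must pass.
- A reader might infer that the trial tolerates no attrition at all. That is so only if the full 15% are also non-compliant and each effect must pass its own interaction test. With no interaction test, power is still 79.9% at 10% missing.
- A reader might infer that no woman who exits is scored. Women who only stop the intervention are followed and analysed (section 7.8.2). A woman who leaves after Visit 2 already has her OGTT result. A voluntary withdrawer is to have the section 7.6.3 assessments, which include a fasting glucose, though off schedule and without an OGTT.

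Pregnancy loss or delivery before 26 weeks would also leave no result. Sections 7.8 and 7.9 do not list it, so the point does not rest on it.

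**Conclusion.** The point holds as an unstated assumption with a modest effect. The 80% at 1,856 is correct only if every randomised woman has a GDM result, while the protocol foresees unreplaced exits without one. If such losses are additional to 15% non-compliance, each 5% missing costs roughly 2 points, down to about 74% at 15%. If they fall within the 15%, the stated size is sufficient. The document does not say which applies, since it defines all 15% as non-compliant. The figures assume the cell risks of section 10.2, outcomes missing equally across arms and unrelated to risk, no true country interaction, and each effect passing its own interaction test. The missing rates are illustrative.

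**What to change.** In section 10.2:

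- Label the 15% as non-compliance with the outcome observed, and state whether it is also meant to cover women without a GDM result.
- If it is, give the assumed split and the power that follows.
- If it is not, add the missing-outcome rate as a separate input, with a range such as 5-15%. Restate the power at 1,856 randomised over that range, with the expected number of scored women.
- Reconcile 1,856 with the 1,875 in the synopsis.

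The cost is a rerun of the existing simulation with one more parameter and, if losses are additional, a slightly less favourable stated power. No extra enrolment is needed.
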